### Concealment mechanisms {16b}

The randomization will be carried out via EnnovClinical software by connecting to the website: https://nantes-lrsy.hugo-online.fr/. The connection will be made using a login, a password, and a study number, issued by a data manager of the Sponsor Department of CHU Nantes. The inclusion number and arm of randomization will be assigned automatically.

### Implementation {16c}

The randomization key is known only to the biostatistician, who will not participate to the study, and the data managers, to make it impossible for the investigator to assign a particular treatment.

### Assignment of interventions: blinding

#### Who will be blinded {17a}

Our studies are randomized double-blinded trials. The patients and the investigators and their teams will be blinded and will not know the treatment assigned. As Karanicolas et al. pointed out in their article from 2010, their study should have been masked to the biostatisticians until analyses had been performed, to reduce the study bias [28].

#### Procedure for unblinding if needed {17b}

Under normal circumstances, blind should not be broken until all patients have completed the study and the database is locked. In the current study, the investigator does not need to know the treatment arm of the patient in case of adverse event, as the treatment will be symptomatic and not adapted to the arm. The blind will be broken only by the pharmacovigilant team for safety purposes and transmission. This will be done according to the internal sponsor’s procedure.

## Data collection and management

### Plans for assessment and collections of outcomes—description of the parameters for evaluating efficacy {18a}

All examinations will be performed by the investigator or a qualified member of the investigational staff. Firstly, he will make a full physical examination which includes the following assessments: cardiovascular, head-ear-nose-throat, eyes, gastro-intestinal, general appearance, lymph nodes, musculoskeletal, neurological, respiratory, skin, and mucous membranes. Body weight and height will be measured.

Any abnormalities present at inclusion, or subsequent changes, will be documented in the appropriate sections of the eCRF. Any clinically significant abnormalities persisting at the end of the study will be followed by the investigator until resolution or until reaching a clinically stable endpoint. Vital signs and respiratory status will be reported. A 12-lead digitalized ECGs will be recorded according to the study schedule while the patient is in supine position for at least 5 min. ECG is performed at inclusion visit; other ECG will be performed at the discretion of the investigator, as deemed necessary for appropriate patient care.

Clinical patient status will be assessed by a seven-level ordinal scale (with levels ranging from one to seven and higher scores indicating a worse condition). This scale will be assessed at each study visit. Each day, the worse score for the previous 24 h will be recorded, i.e., on day 3, day 2 score is obtained and recorded as day 2. On day 1 and day 5, assessment will have to be performed before XAV-19 infusion.

We will use also NEWS2 which is the latest version of the National Early Warning Score (NEWS), updated in December 2017 [20], which advocates a system to standardize the assessment and response to acute illness. NEWS2 is based on a simple aggregate scoring system in which a score is allocated to physiological measurements, already recorded in routine practice, when patients present to, or are being monitored in hospital. Six simple physiological parameters form the basis of the scoring system: (1) respiration rate, (2) oxygen saturation, (3) systolic blood pressure, (4) pulse rate, (5) level of consciousness or new confusion, and (6) temperature. A score is allocated to each parameter as they are measured, with the magnitude of the score reflecting how extremely the parameter varies from the norm. The score is then aggregated and uplifted by 2 points for people requiring supplemental oxygen to maintain their recommended oxygen saturation.

### Plan to promote participant retention and complete follow-up {18b}

As a reminder, the target population will be hospitalized; missing data could only result of withdrawal of the consent or a serious adverse event (SAE). No plan to promote participant retention has been realized.

### Data management {19}

For each patient, a case report form (CRF) is created which includes the data necessary to ensure compliance with the protocol and all data necessary for the statistical analysis and to identify major protocol deviations. Data collection is done directly by the investigator or clinical research associate in charge of the study, using an electronic CRF (eCRF) developed by the Sponsor Department of the CHU Nantes with ENNOV Clinical. The data are encoded to keep the identities of the patients confidential.

### Confidentiality {27}

Data collected during the study will be processed electronically in compliance with the requirements of the CNIL (compliance with the French Reference Methodology MR001). The CNIL is an independent French administrative regulatory body whose mission is to ensure that data privacy law is applied to the collection, storage, and use of personal data.

### Plans for collection, laboratory evaluation, and storage of biological specimens for genetic or molecular analysis in this trial/future use {33}

For the pharmacokinetics analysis, blood samples will be collected at each draw for specific analysis as described below according to the study schedule. These analyses will be run under Good Laboratory Practices conditions. In the phase 2a, all patients included in the study will have pharmacokinetic samples taken.

For the immunological analyses, blood samples will be collected for specific analysis as described below according to the study schedule. Actual time and date of blood drawn must be accurately recorded on the eCRF.

The following analyses will be performed:
T and B lymphocyte sub-populations (spectral flow cytometry)Tfh-B cell interactionTranscriptomic analysis on PBMC and B cellsSpike/ACE2 interaction neutralizing antibodySerum cytokines: MCP1, IP10, IL-10, IFNα, TNF-α, IL-1b, IL-6, IL-82 (in the phase 2a) and IL-6, IFNa2, IL-10, IP10, CCL2 (in the phase 2b)

Finally, the transcriptomic analyses of messenger RNA molecules will be extracted from peripheral blood in order to identify transcripts that are specifically over- or under-expressed in correlation with the clinical status and with viral load. The goal is to identify possible biomarkers of the disease severity and disease responding to the treatment and, using deconvolution bioanalyses, also identify cell population changes in complement to the direct flow cytometry analyses. A focus will be made on B cell sub-populations and their role in interaction with Tfh cells. These immunological analyses will be performed by the CRTI in Nantes University (INSERM U1064) (led by [name], CNRS).

At the end of the study, residual biological samples resulting from sampling (blood sample) for all patients from phase 2a and only for patients accepting to participate to the immunomonitoring study in the phase 2b will be kept. In the latter case, the subject’s written consent will be collected at screening and the samples stored will be integrated into the biocollection “POLYCOR” located in the Centre de Ressources Biologiques (CRB) of the CHU Nantes, under the responsibility of [name]. This biocollection will be attached to the “Immunologie” research program declared on 05/09/2011 under the no. DC-2011-1399 and in the following amending declarations (DC-2012-1555; DC-2013-1832, DC2014-2206, and DC-2017-2987 currently pending) at the Ministry of Research and having obtained a favorable decision from the CPP Ouest VI (Ethics Committee) on 7 April 2015.

## Statistical methods

### Statistical methods for primary and secondary outcomes {20a}

For the phase 2a study, the safety population included all subjects randomized into the study who received at least one dose of study drug. The intention-to-treat (exposed, ITT[E]) Population was defined as all subjects who met study criteria and were randomized into the study with documented evidence of having received at least one dose of randomized treatment and at least one post-baseline XAV-19 IgG SARS-CoV2 titer measurements. The Per-Protocol Population was defined as all subjects included in the ITTE Population excluding those who had at least one major protocol deviation.

The primary endpoint will be evaluated for ITTE Population by a Kruskal-Wallis test between all placebo patients and all treated patients.

Groups of treatment will be described according to variables in of the secondary endpoints. Categorical variables will be summarized by percent and continuous variable by means and standard error, and medians and interquartile range.

For the phase 2b, categorical variables will be summarized by percent and continuous variable by means and standard error, and medians and interquartile range. Survival rate and duration of oxygen therapy will be compared between the two groups for the primary endpoints.

For the secondary endpoint, quantitative endpoint will be compared using linear mixed model and qualitative data with logistic mixed model to take into account stratification factors. Time data’s will be analyzed using survival model. Fine and Gray method will be used to take into account competing risk.

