#### POLYCOR study

Knowing GH-pAbs are well tolerated in human and that neutralizing Abs can be an effective therapeutic approach during SARS disease, the POLYCOR aims to address, in randomized double-blinded, placebo-controlled study the efficacy of polyclonal humanized anti-SARS-CoV2 antibodies (XAV-19) in patients with COVID-19-induced moderate pneumonia.

POLYCOR is divided into 2 steps: the phase 2a will be a double ascending dose (DAD), double-blinded, placebo-controlled randomized study to select the optimal dose of XAV-19 for the phase 2b. The phase 2b (double fixed dose (DFD)) will be a double-blinded, placebo-controlled randomized study to assess clinical benefit and safety of the phase 2a selected dose of XAV-19 in 352 hospitalized adults with COVID-19-associated moderate pneumonia.

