### Objectives {7}

#### The objectives of phase 2a study

The primary objectives are to (1) evaluate the titers of XAV-19 in treated patients versus placebo-treated patients at day 8 and (2) assess the safety and tolerability of XAV-19.

The secondary objectives of the study are to (1) characterize pharmacokinetics (PK) of XAV-19 infected patients over the time from D1 to D29, (2) evaluate the antibody titers of XAV-19 and to compare group 1 treated patients versus group 2 treated patients at day 8, and (3) describe groups of patients according to clinical variables (duration of supplemental oxygen, transfer in intensive care unit (ICU), normalization of fever, titer of biomarkers, ordinal scale assessed at day 15, hospital length of stay).

Exploratory objectives will be to assess the effects of neutralizing antibodies use on virus-induced immune response on longitudinal follow-up and to identify targets for “immuno-monitoring” for the next phase of the study and to investigate the immunogenicity of COVID-19 during treatment with XAV-19.

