#### The objectives of phase 2b study

The primary objective of the study is to compare duration until weaning supplemental oxygen in the two groups of treatment before or at day 15.

The secondary objectives of the study are the comparison between two groups of:
Evolution of National Early Warning Score (NEWS 2) [20]Changes in the 7-point ordinal scale between baseline and day 15Improvement of one category from admission using the 7-point ordinal scaleNormalization of feverDuration of oxygen therapy over 29 daysOxygen requirement over 29 daysTime to weaning in supplemental oxygen and proportion without O2 requirement at D15Transfer to ICU with need for invasive mechanical ventilation or high flow O2Hospital length of stayAll cause of mortalitySafety of XAV-19

To note*,* two ancillary studies will complete the phase 2b. For the pharmacokinetic study, 16 patients will be included, as for the immuno-monitoring study 30 patients will be included. Analyses performed will be identical to those performed in the phase 2a study.

Study sites involved in these ancillary studies will propose to their first patients to participate to these studies. Patients can participate simultaneously to both studies.

The objective of the pharmacokinetic study is to characterize pharmacokinetics (PK) of XAV-19-infected patients over time from D1 to D29. Pharmacokinetic analysis corresponds to antibody titer measurements at day 1 (pre-dose, post-dose), day 3, day 5 (pre-dose, post-dose), day 8, day 15, and day 29.

Objectives will be to assess the effects of neutralizing antibodies use on virus-induced immune response on longitudinal follow-up and to identify targets for “immuno-monitoring” for the next phase of the study and to investigate the immunogenicity of COVID-19 during treatment with XAV-19.

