Clinical experience with LIS1 glyco-humanized swine IgG administration. LIS1 is an experimental lymphodepleting polyclonal swine antibody produced by the glyco-humanized GH-pAb platform of Xenothera Laboratory. It is currently in clinical development in kidney transplant patients in EU (EUDRACT 2019-000917-35). So far, the maximal dose that has been reached in the escalating dose arm and found acceptable by the DSMC (which recommended pursuing the trial at this dose) is five daily administrations of 8 mg/kg, i.e., a cumulated dose of 40 mg/kg. Therefore, in this first-in-human trial with XAV-19, we have proposed that the cumulative dose stays inferior to the maximal LIS1 dose administered.Published clinical experience gained with use of convalescent plasma (CP) containing anti-COVID-19 neutralizing antibodies, having evidenced improvement of clinical symptoms. First, critically ill patients with COVID-19 received two consecutive transfusions with 200 mL CP. CP had a SARS-CoV-2-specific antibody (IgG) binding titer greater than 1:1000 and a neutralization titer greater than 40 (end point dilution titers) [9]. In this experience, the ratio between binding and neutralization titers is therefore of 25-fold on the average. Second, Duan et al. treated 10 COVID-19 patients with one dose of 200 mL CP [21]. In this report, the average neutralizing titer calculated on 40 CP was > 1/160. Third, in a former clinical experience with 80 CP transfusions from SARS-convalescent patients in 2003, the average CP volume was 279 mL and the neutralizing titer was > 1/160 [22]. Thus, all together, estimating that transfusion of 200 mL CP corresponds to 25 mg/kg IgG (considering that plasma contains 10 mg/mL IgG and considering 80-kg patients), we can postulate that 25 mg/kg of an IgG preparation presenting a neutralizing titer of at least 1/40 presents a clinical interest. Binding and neutralization titers of glyco-humanized serum from which XAV-19 has been obtained were of approximately 1/100,000 and 1/4000 (in the ELISA neutralization assay). The neutralization titer in a cytopathogenic effect assay was of 1:1600. This neutralizing titer of XAV-19 is thus 40- to 100-fold higher (depending on the assay) as compared with COVID-19 CP presenting a clinical interest according to the literature, and 12.5-fold higher than recommended by the European Commission. It has been considered that the ratio of the neutralization titer in XAV-19 vs CP should be used in the dose selection. According to available data, a batch exhibiting a 40-fold ratio to CP might thus be used at a 40-fold inferior dose, which means that infusions of 0.6 mg/kg XAV-19 should result in similar effects in vivo as compared with 25 mg/kg CP. Recent guidance from the European Commission on use of CP revised desired neutralizing titers of CP and suggested that “neutralizing antibody titers should optimally be greater than 1:320, but lower thresholds might also be effective” (https://www.phc.org.ua/sites/default/files/users/user90/Guidance_plasma_covid19_en.pdf). Therefore, another, higher dose than 0.6 mg/kg XAV-19 might also be tested.PK/PD information obtained from ex vivo assessment of XAV-19. XAV-19 has been assessed in competition ELISA (inhibition of the COVID-19 spike protein binding to ACE-2 receptor) and tested in neutralizing activity assay against SARS-CoV-2 using classical plaque reduction test using Vero cells. Our data showed an IC_50_ (concentration for reaching 50% of maximal signal in the test) of approx. 2.5 μg/mL of the first batch of XAV-19 in these ELISA and neutralization assays [14]. Data from the cytopathogenic effect assay showed a complete inhibition of SARS-CoV-2 infectivity was reached around 15–25 μg/mL in the assay. Considering an average plasma volume of 38.5 mL/kg, infusions of 0.96 mg/kg of this batch of XAV-19 would be required to reach (at Cmax) 25 μg/mL plasma concentration (at Cmax). The volume of distribution of swine glyco-humanized IgG measured in primates (53 mL/kg) has a value close to that of the plasma suggesting that the XAV-19 IgGs will essentially circulate in the plasma. Considering also distribution and elimination half-life, estimated at 172 h in primates, we can select an initial dose 2-fold higher than this target, given on day 1 and day 5, so as to stay above a through level of 25 μg/mL over more than a week, a duration deemed appropriate to obtain a clinical response. The estimated dose to reach this target is 2 mg/Kg.

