
Based on these 3 datasets, the Pharmacologically Active Dose (PAD) Standard of Care SOC for Group 2 of phase 2a would be 2 mg/kg infused on day 1 and on day 5 for a batch of XAV-19 presenting the IC_50_ of 2.5 μg/mL in the ELISA Spike/ACE2 neutralization assay. It is meant to maintain trough levels of XAV-19 above 25 μg/mL over several days. This dosing is lower than the dose already administered in human in the previous clinical experience demonstrating safety with LIS1 (5 daily administrations of 8 mg/kg, thus a total of 40 mg/kg), thus lower than a dosing which might reach a dose limiting toxicity. In other words, this dosing (two administrations of 2 mg/kg) presents a 10-fold safety factor for the first administration of XAV-19, as compared with previous experience with glyco-humanized swine IgG. Based on this PAD, the first-in-human dose (group 1 of phase2a) can be set with a safety factor of four following the escalation guidelines of the European Commission. For the first-in-human dose, 0.5 mg/kg on day 1 and on day 5 is therefore proposed, i.e., a cumulated dose of 1 mg/kg. Thus, there is a 4-fold increment between group 1 and group 2 in the phase 2a.

The evaluation of safety and phamacokinetic parameters in both dosing groups will guide the choice for the dose to be used in the phase 2b study.

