### Methods for additional analyses (e.g., subgroup analyses) {20b}

The PK Concentration Population included all subjects who received XAV-19 at least once during the study. The PK Summary Population included subjects with an evaluable pharmacokinetic profile of XAV-19 on day 8. The PK/PD Summary Population included subjects who met the criteria for both PP Population and PK Summary Population.

The pharmacokinetic analysis will be evaluated by the study of the accumulation, time-invariance, achievement of steady state, and dose-proportionality by ANOVA models with terms for subjects as a random effect and day as fixed effect.

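### The phase 2a PK model meant to study dose-proportionality has no dose term, the primary titre test pools both doses, and the one exposure comparison between doses is secondary, descriptive and set at two different days

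*Protocol article*

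**What the plan says.** The section on the POLYCOR study gives the purpose of phase 2a: "to select the optimal dose of XAV-19 for the phase 2b". The rationale for the comparators (item 6b) adds that safety and pharmacokinetic parameters in both dosing groups "will guide the choice for the dose to be used in the phase 2b study". It also gives the exposure target behind the group 2 dose, which was chosen "so as to stay above a through level of 25 μg/mL over more than a week".

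The first primary objective of phase 2a is to "evaluate the titers of XAV-19 in treated patients versus placebo-treated patients at day 8". The matching test in the statistical methods (item 20a) is: "The primary endpoint will be evaluated for ITTE Population by a Kruskal-Wallis test between all placebo patients and all treated patients".

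Item 20b lists accumulation, time-invariance, steady state and dose-proportionality as the aims of the pharmacokinetic analysis, and describes the last as "dose-proportionality by ANOVA models with terms for subjects as a random effect and day as fixed effect". No dose or group term is listed.

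The doses are compared on exposure in one other place. A secondary objective compares treated patients of groups 1 and 2 at day 8, while the corresponding secondary endpoint in the Outcomes section (item 12) places those titres at day 15. For secondary endpoints item 20a plans description by treatment group.

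For the phase 2b ancillary studies the plan says: "Analyses performed will be identical to those performed in the phase 2a study". Phase 2b uses one selected dose.

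**The concern.** The two analyses of exposure that the plan specifies in any detail do not fit the question phase 2a has to answer. A comparison of all treated with all placebo patients shows that titres differ after infusion, whichever dose produced the difference. A model without a dose term cannot yield the dose-proportionality it is named for. The comparison that does bear on dose has two different days and no estimate or interval attached.

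At stake is how well the exposure evidence behind the phase 2b dose can be read. An analyst who follows item 20b literally would report day effects and a subject variance under the heading of dose-proportionality. An analyst choosing between day 8 and day 15 after seeing the data could report either and still be following the plan.

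**Working it through.** **Group sizes.** Item 16a gives, per cohort, two patients at 1:1 and six at 1:5 (placebo to active). Active: 1 + 5 = 6. Placebo: 1 + 1 = 2. Two cohorts give 12 active (6 per dose), 4 placebo and 16 in all, which reproduces the figure in the Sample size section.

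**The pooled test.** If every treated value exceeds every placebo value, the exact two-sided p-value is 2/C(16,4) = 2/1820 = 0.0011. The large-sample Kruskal-Wallis p-value with all placebo values tied at zero is 0.0034. In 2,000 simulated trials per setting (assumed: log-normal day-8 titres, between-patient CV of 30%, 50% or 100%, placebo at zero, alpha 0.05), the test rejected in 100% of runs whether the true group 2/group 1 ratio was 1, 2 or 4. If the assay also detected patients' own antibodies, placebo would not be zero and the rejection rate could fall, but a pooled result still could not be attributed to either dose.

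**The ANOVA.** Write log exposure of patient i on day j as μ + u(i) + day(j) + error. Dose is constant within a patient, so a dose effect can enter only through μ and the spread of u. With half the patients shifted by ln 4 = 1.386, the expected addition to the variance of u is 1.386²/4 = 0.48. One simulated data set (12 patients, six sampling days, the same random draws under both ratios) shows this:

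| True group 2/group 1 ratio | Day effects, days 3 to 29 against day 1 | Intercept | Between-subject variance, no dose term | Between-subject variance, dose term added |
|---|---|---|---|---|
| 1 | −0.125, −0.277, −0.318, −0.609, −1.424 | 0.094 | 0.11 | 0.10 |
| 4 | identical | 0.787 | 0.82 | 0.10 |

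The rise of 0.71 exceeds 0.48 because, in this sample, the random patient effects happened to favour group 2. With the dose term the estimated ratio was 1.28 under a true ratio of 1 and 5.13 under a true ratio of 4. The two differ by the factor of 4 that was put in (5.13/1.28 = 4.0). Without the term there is no such estimate.

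**What six against six can show.** The smallest exact two-sided p-value for group 1 against group 2 is 2/C(12,6) = 2/924 = 0.0022. The interval for the ratio of geometric means follows from σ = √ln(1 + CV²), SE = σ√(2/6) and t(10 df) = 2.228. CVs are assumed.

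| CV | σ | SE | CI factor, exp(2.228·SE) | 95% CI if the estimate is 4 | Power, true ratio 4 | Power, true ratio 2 |
|---|---|---|---|---|---|---|
| 30% | 0.294 | 0.169 | 1.46 | 2.7 to 5.8 | about 100% | 93% |
| 50% | 0.472 | 0.273 | 1.84 | 2.2 to 7.3 | 99% | 58% |
| 100% | 0.833 | 0.481 | 2.92 | 1.4 to 11.7 | 66% | 23% |

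The power columns come from the simulated Kruskal-Wallis test of 6 against 6.

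**Sampling times against the target.** Item 6b gives, from primates, a volume of 53 mL/kg and a half-life of 172 h. Assuming one compartment, the first infusion gives 500/53 = 9.4 and 2000/53 = 37.7 μg/mL for 0.5 and 2 mg/kg. Decay is 2^(−t/172), and the second infusion is at 96 h.

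- Day 5 pre-dose: × 0.679, giving 6.4 and 25.6.
- Immediately after the second infusion: 15.8 and 63.4.
- Day 8 (72 h later): × 0.748, giving 11.9 and 47.4.
- Day 15 (240 h later): × 0.380, giving 6.0 and 24.1.

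On this model the higher dose falls to 25 μg/mL at 96 + 172·log2(63.4/25) = 327 h, about day 14.6. The day-5 trough is close to the target, and day 8 puts the two doses on opposite sides of it.

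**The case against.** The strongest reply is that dose selection was never assigned to the pooled test. That test matches the first primary objective, and the plan has other sources of dose-level information: the secondary group 1 versus group 2 objective, serial sampling from day 1 to day 29, description by treatment group, and a primary tolerability endpoint comparing the two treated groups. Item 6b names safety and pharmacokinetics in both dosing groups as the basis of choice, and the monitoring committee must approve the step to phase 2b. This stands. A reader might infer that the plan contains no analysis of exposure by dose; the documents do not support that.

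A reader might also infer that day 8 is the wrong time and that the target is decided at day 15. The figures above do not bear this out. The stated target is more than a week, not two weeks; day 8 discriminates well between the doses, and on the plan's own inputs the higher dose stays above 25 μg/mL until about day 14.6. Only the day-5 pre-dose trough is a fair addition.

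A third tempting reading is that steady state cannot be reached with two infusions. That rests on a primate half-life, and human kinetics are what phase 2a measures. The plan says it will study steady state, not that it will be achieved.

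Finally, item 20b is one sentence in an article that condenses the methods, and the phase 2b statement about identical analyses covers two ancillary studies and is followed by a definition in terms of titre measurements. That makes the phase 2b point a wording matter. It does not rescue the ANOVA: the model terms are stated, and they cannot deliver the stated aim.

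**Conclusion.** The ANOVA in item 20b is wrong as written. Dose varies only between patients, the model has no dose term, and a dose effect of any size goes into the intercept and the between-subject variance (0.11 to 0.82 in the example). This follows from the design and needs no assumption about the data.

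The primary titre test shows treated-versus-placebo separation only and cannot inform the choice between doses. It is legitimate for its own objective. The 100% rejection rate assumes that placebo values are zero; the inability to separate the doses does not.

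Exposure by dose is planned, but only as a secondary, descriptive comparison whose day differs between objective and endpoint. The weakness therefore lies in how the dose comparison is specified; it is not absent. The correction is small in wording and worth making, because the analysis named for dose-proportionality would otherwise return no answer.

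**What to change.** 1. In item 20b, analyse log-transformed exposure (AUC and Cmax) with dose group, or log dose, as a fixed effect. Report the group 2/group 1 ratio with 95% CI against 4. Keep the subject random effect only where a patient contributes more than one value, such as Cmax after each infusion.
2. Report titres per dose group with intervals at the times already sampled, including day 5 pre-dose and day 8, against the plan's own 25 μg/mL target. State how titres convert to μg/mL if the assay does not report that unit.
3. Reconcile day 8 (objective) with day 15 (endpoint) for the group 1 versus group 2 comparison.
4. Keep the pooled test as the answer to the first primary objective, stating that it does not bear on dose.
5. State that dose-proportionality is excluded from the identical analyses of the phase 2b ancillary pharmacokinetic study, which has a single dose.

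The Trial status section says phase 2a is complete, so items 1 to 4 concern analysis and reporting of samples the plan already collected. The cost is a little more analysis. The limit is precision: with 6 patients per dose, an estimated ratio of 4 carries an interval of about 2.2 to 7.3 at an assumed CV of 50%, so the result should be read as an estimate rather than a test.
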